### 2.7. Melatonin and 6-Hydroxymelatonin Determination via Ultraperformance Liquid Chromatography Coupled to Mass Spectrometry

Urinary and salivary concentrations of melatonin and of its main metabolite 6-hydroxymelatonin will be measured in samples collected from all patients by using a validated LC-MS method with minor modifications [16].

Urinary and unstimulated oral fluid samples will be taken 30 min after the EEG. Urine samples will be collected in a 50 mL polypropylene tube. Samples will be centrifuged at 17,000× *g* for 10 min and the supernatants will be transferred in 10 mL tubes. Oral fluid sampling will be obtained via passive drooling, aspirated with a syringe, and transferred into 2 mL polypropylene tubes. Subjects will be instructed to not eat/drink for 30 min before sample collection and to rinse their mouths with plain water. All samples will be stored at −80 °C until analysis.

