## Abstract

Electroencephalography (EEG) continues to be a pivotal investigation in children with epilepsy, providing diagnostic evidence and supporting syndromic classification. In the pediatric population, electroencephalographic recordings are frequently performed during sleep, since this procedure reduces the number of artifacts and activates epileptiform abnormalities. To date, no shared guidelines are available for sleep induction in EEG. Among the interventions used in the clinical setting, melatonin and sleep deprivation represent the most used methods. The main purpose of this study is to test the non-inferiority of 3–5 mg melatonin versus sleep deprivation in achieving sleep in nap electroencephalography in children and young adult patients with epilepsy. To test non-inferiority, a randomized crossover trial is proposed where 30 patients will be randomized to receive 3–5 mg melatonin or sleep deprivation. Each enrolled subject will perform EEG recordings during sleep in the early afternoon for a total of 60 EEGs. In the melatonin group, the study drug will be administered a single oral dose 30 min prior to the EEG recording. In the sleep deprivation group, parents will be required to subject the child to sleep deprivation the night before registration. Urinary and salivary concentrations of melatonin and of its main metabolite 6-hydroxymelatonin will be determined by using a validated LC-MS method. The present protocol aims to offer a standardized protocol for sleep induction to be applied to EEG recordings in those of pediatric age. In addition, melatonin metabolism and elimination will be characterized and its potential interference in interictal abnormalities will be assessed.

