### 2.3. Participants

Subjects will be screened by using the following inclusion criteria: (i) children and young adults with epilepsy aged between 4 and 18 years with normal psychomotor development; (ii) stable seizure frequency in the 3 months preceding the study; (iii) stable antiseizure medication (ASM) treatment in the 3 months preceding the study; and (iv) written informed consent from parents or the legal representative.

Exclusion criteria are as follows: (i) subjects diagnosed with obstructive sleep apnea or sleep disturbances; (ii) history of neurodevelopmental disorders; (iii) concomitant use of hypnotics, stimulants, systemic corticosteroids, or other immunosuppressants; (iv) history of daily melatonin use; (v) any condition which, in the opinion of the investigator, would compromise the achievement of the objectives of the study; and (vi) failure to obtain the informed consent.

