### 2.4. Interventions

Melatonin will be compared to sleep deprivation. Patients who fulfill the inclusion criteria will be randomly allocated to receive melatonin or sleep deprivation as the first intervention. One–three months after the first EEG recording, the crossover will take place. Melatonin oral solution at the dose of 3 or 5 mg depending on body weight (3 mg for patients < 15 kg; 5 mg for patients > 15 kg) will be used as the study medication. Melatonin will be administered as a single dose 30 min before the EEG recording. Sleep deprivation will be represented by sleep deprivation of 50% of physiological sleep the night before EEG registration. The investigator a week before the EEG test will contact the patient’s caregiver. The telephone call will be devoted to investigating the patient’s sleep habits in terms of mean amount of sleep per night, excluding the presence of concomitant sleep disturbances. Based on the reported mean sleep time per night, caregivers will be instructed to deprive 50% of sleep the night before the EEG. Moreover, caregivers will be asked to not let patients perform naps in the morning of the examination or on their way to the hospital. Each EEG recording will be performed at the same hour, in the early afternoon (1:30 p.m.). The EEG recording will last 1 h. All EEG recordings will be performed in a dark and quiet room, and patients will be instructed to lie calmly and try to sleep. EEG electrodes will be placed on the patient’s scalp surface according to the 10/20 system. Polygraphic channels including ECG and respiration will be recorded for all participants. Electromyogram activity will be recorded according to the patient’s epileptic syndrome.

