
Doses of melatonin were administered at different dosages depending on age in most of the studies, varying between 2 mg and 10 mg [12,17,22,23,24,25].

There are no studies on the potential dose-dependent effects of melatonin during acute use as a hypnotic in children. Based on our clinical experience, we will administer melatonin according to body weight (3 mg for patients < 15 kg; 5 mg for patients > 15 kg). Our choice to not exceed 5 mg is supported by the observation by Eiserman and colleagues [25] that the administration of higher doses of melatonin showed comparable success rates in hypno-induction with regard to lower doses [22,23,24]. The timing of melatonin administration reported in different studies is substantially variable, ranging from 30–40 min before EEG recording [12], 15 min before electrode application [24], or at the time of electrode application [22,23]. We will provide melatonin 30 min before EEG execution because when exogenous melatonin is administered, it reaches peak plasma concentration in 20–120 min, and its sleep onset effect appears 30–35 min after drug administration [11]. Additionally, the extent of sleep deprivation is extremely variable, ranging from a few hours to almost 10 h. Even within single studies, the timing and extent of sleep deprivation might be inconstant [23]. The approximate need for sleep varies significantly from childhood to adolescence [26]. It is estimated that in preschool children, nocturnal sleep time begins to average at 10 h, whereas as children grow up, nocturnal sleep time decreases, becoming 8 h per night in adolescence. A variety of factors influence sleep duration in children, adolescents, and young adults, including generational trends, societal pressures (such as school start times), and familial habits [27]. Taking this huge variability in mind and considering the wide age range of enrolled patients, our choice is not to establish rigid times for going to bed and waking up before the EEG, but to provide a more flexible indication, represented by the deprivation of 50% of physiological sleep for each single patient. Additionally, nap EEGs are usually performed at variable times of the day [23,24] or the time of execution is not specified [17]. Although there are no clear data on the best time of day to perform nap EEGs, in the context of our protocol, we have decided to perform all EEG recordings in the noon session to exploit the “afternoon nap zone” of the physiological circadian rhythm [28]. Although melatonin appeared to be non-inferior compared with sleep deprivation in previous studies, variability in melatonin dosing and timing and differences in the application of sleep deprivation and subject selection, as well as other factors such as environmental differences and the study population, have so far prevented the drawing of a solid conclusion and the provision of a hypno-induction protocol shared among the different pediatric neurophysiology centers. Our study was developed according to a randomized crossover non-inferiority design to provide evidence for a standardized protocol to be used in the routine clinical setting for sleep induction in nap electroencephalography. Furthermore, the thorough estimate of the main metabolite 6-hydroxymelatonin will allow us to further characterize melatonin metabolism and elimination, providing useful information on the optimal dose and time of administration. The findings of the proposed trial will ultimately establish melatonin interference in interictal abnormalities during acute use as a hypnotic agent.

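### One post-dose sampling time, about 2 h after melatonin, cannot support the stated aims of characterising elimination and informing the optimal dose and time of administration

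*Protocol article*

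**What the plan says.** **Dosing and recording.** Section 2.4: "Melatonin will be administered as a single dose 30 min before the EEG recording", and "The EEG recording will last 1 h". Every patient has the same nominal dosing time relative to the EEG. The dose is assigned by weight: "3 mg for patients < 15 kg; 5 mg for patients > 15 kg". Section 2.3 admits patients "aged between 4 and 18 years with normal psychomotor development".

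**Sampling.** Section 2.7: "Urinary and unstimulated oral fluid samples will be taken 30 min after the EEG". No other sampling time is given. Melatonin and 6-hydroxymelatonin are to be measured in both urine and saliva.

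**What the samples are for.** The Abstract states that "melatonin metabolism and elimination will be characterized". The Discussion says that estimating the metabolite "will allow us to further characterize melatonin metabolism and elimination, providing useful information on the optimal dose and time of administration".

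**Peak time.** To justify the dosing time, the Discussion says of exogenous melatonin that "it reaches peak plasma concentration in 20–120 min".

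Melatonin and metabolite levels are not among the primary or secondary outcomes in Sections 2.5 and 2.6.

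**The concern.** The sampling scheme and the stated purpose are both explicit, and they do not match. An elimination rate is the slope of the declining part of a concentration curve, and a slope needs at least two points after the peak. The scheme gives one point, and the protocol's own peak range does not establish whether that point lies at the peak or well past it.

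Information on the best time of administration needs variation in that time, and there is none by design. Information on the best dose needs dose to vary independently of the patient, whereas here weight determines it.

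What is at stake is interpretation. Differences between children in one 2-h value could be reported as differences in elimination when they reflect how fast the drug was absorbed. Such a reading could then feed into the standardised induction protocol that the trial is meant to provide.

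**Working it through.** The document states no pharmacokinetic figure or precision target, so there is none to reproduce. The check is of timing and identifiability.

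**Step 1: dose-to-sample interval.** Inputs from Sections 2.4 and 2.7: dose to EEG start 30 min, EEG 60 min, EEG end to sample 30 min.

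30 + 60 + 30 = 120 min.

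(If the sample were timed from the start of the EEG, it would be 30 + 30 = 60 min, still a single point.)

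**Step 2: position relative to the peak.** With a peak at 20–120 min (Discussion), the sample falls between 120 − 120 = 0 and 120 − 20 = 100 min after the peak. The range is given for plasma; the article gives none for saliva or urine.

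**Step 3: unknowns against data.** The simplest oral model is one-compartment with first-order absorption:

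C(t) = A · ka/(ka − ke) · [exp(−ke·t) − exp(−ka·t)], where A = F·Dose/V.

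It has three unknowns (A, ka, ke) and one concentration per matrix, at t = 2 h. Half-life is not in the document, so I assumed 0.5–3 h and took the peak at 20, 40, 60 or 120 min. Every combination reproduces the same 2-h concentration if A is rescaled. For C(2 h) = 1, the required A runs from 1.46 (half-life 3 h, peak 60 min) to 16.00 (half-life 0.5 h, peak 120 min), a ratio of 16.00/1.46 ≈ 11. For example, with the peak at 60 min, half-lives of 0.5 h and 1 h give the same 2-h value when A is 5.33 and 2.67: a twofold difference in scale hides a twofold difference in half-life.

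**Step 4: how far peak timing alone moves the 2-h value (illustration only).** Hold A and ke fixed, and let the peak move over 20–120 min by changing ka. The quantity is C(2 h)/A.

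| Assumed half-life | Peak 20 min | Peak 60 min | Peak 120 min | Largest/smallest |
|---|---|---|---|---|
| 60 min | 0.2736 | 0.3750 | 0.2500 | 1.5 |
| 45 min | 0.1815 | 0.2923 | 0.1575 | 1.9 |
| 30 min | 0.0833 | 0.1875 | 0.0625 | 3.0 |

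A finer grid of peak times, every 5 min, leaves the last column unchanged to one decimal.

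If the later peak instead came from a pure delay, with the same curve shifted by 100 min at the same height, the ratio would be 2^(100/half-life): 2^(100/60) = 3.2, 2^(100/45) = 4.7 and 2^(100/30) = 10.1.

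**Step 5: contrasts for dose and time.** There is one administration time, hence no contrast. There are two dose levels, each fixed by a weight band, and one dose above 15 kg. Dose per kg therefore varies only because weight varies, and no comparison at a given weight is possible.

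**The case against.** Four points can be made for the plan.

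**The wording is soft.** The Discussion offers useful information on dose and time and does not promise a half-life or a dose determination. That is fair and lowers the severity. The Abstract, however, says without qualification that elimination will be characterised, and soft wording does not create a timing contrast that the design lacks.

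**Metabolism is partly addressed.** Measuring parent and metabolite together gives a ratio that says something about metabolism at 2 h. This stands, so the concern does not extend to the metabolism half of the aim.

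**Something can be learned about dose.** A reader might infer that the data can say nothing about dose. That goes too far. Children above 15 kg all receive 5 mg, so dose per kg varies, and 2-h levels can be related to sleep latency as exploratory work. The evidence is weak because it is inseparable from body size and the sample is taken after the EEG.

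**Detail may sit elsewhere.** A spot urine concentration depends on dilution and time since the last void, and a reader might fault the article for not mentioning creatinine, void volume or clock times. A condensed article may leave these to the full protocol or laboratory manual, so nothing here relies on them. The sampling time and the aims, by contrast, are stated outright.

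A population model with strong external information could use sparse data. With every sample at the same nominal time it would mainly return what was put in, and the article mentions no such model.

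**Conclusion.** The concern holds for elimination and for optimal time of administration, and in a limited form for optimal dose. One sample per matrix at about 120 min cannot identify an elimination rate under even the simplest oral model. That conclusion needs no assumed half-life.

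The size of the possible misreading does rest on assumptions. With half-lives of 30–60 min, peak timing alone could produce 2-h differences of about 1.5- to 3-fold between children who eliminate melatonin identically, under first-order absorption. A reader might infer a 3- to 10-fold spread from the 100-min gap between the earliest and latest peak. That holds only under a pure absorption delay with equal peak height; with the same dose, volume and bioavailability, slower first-order absorption gives a lower as well as a later peak. These figures also apply a plasma peak range to a point concentration. They do not carry over to urine, which accumulates between voids.

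Nor does the point touch the main result. The measurements are ancillary, do not enter the sample size in Section 2.8, and leave the non-inferiority comparison of sleep latency as it is. The correction is worth making because the claim stands in the Abstract, but the trial does not depend on it.

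**What to change.** In the Abstract and Discussion, restate the aim as an exploratory description of salivary and urinary melatonin and 6-hydroxymelatonin about 2 h after dosing. Present the metabolite-to-parent ratio as a partial indicator of metabolism. Use the same patient's deprivation-day sample as the endogenous reference; Section 2.7 appears to provide one, since it samples all patients after the EEG and each patient has two EEGs. State that this is a reference and not a second post-dose point.

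Drop the claims about elimination and optimal time of administration. Limit any statement on dose to an exploratory association confounded by body size.

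The cost is wording only, with no extra samples and no change to treatment. The downside is a less ambitious pharmacokinetic claim. Keeping the elimination aim instead would need further post-dose sampling times and a timed urine collection with volume, which is a larger burden on the children for an ancillary question.

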### 2.8. Sample Size Calculation

The sample size was calculated based on the primary efficacy endpoint considering the crossover design and the non-inferiority hypothesis. A recent study demonstrated that the combination of sleep deprivation and melatonin was more effective compared to each method alone for inducing sleep [17]. In a previous study, Jain and collaborators demonstrated that melatonin was associated with improvements in sleep latency and wakefulness after sleep onset [18]. In particular, in the latter study, melatonin reduced sleep latency by about 11 min. In both studies, the corresponding calculated 95% confidence lower limit was about −3 min. Given this effect in the two aforementioned studies [17,18] and considering preliminary data at our clinical center, we assume that the clinical limit for no relevant differences in efficacy between the study procedures is −3 min in the sleep latency onset. The sample size was calculated using the formula for non-inferiority crossover studies reported by Julious [19]. A sample of 60 EEGs (30 for each study sequence) to achieve a power of 80% and a level of significance for a one-sided test of 0.025 will be sufficient to demonstrate the non-inferiority of the group treated with melatonin compared with the group of participants randomized to receive sleep deprivation [19].

### 2.9. Randomization

Subjects will be randomly assigned to melatonin or sleep deprivation for the first recording using R software (R Core Team 2021; R Foundation for Statistical Computing, Vienna, Austria) whereby random numbers will be generated. A computerized algorithm will be implemented taking into account the two sequences of the crossover design. A casual assignment to one of the two sequences (sleep deprivation–melatonin and melatonin–sleep deprivation) will be applied without any correction for demographic or clinical factors.

### 2.10. Ethical Considerations

Written informed consent will be obtained from subjects/parents of all subjects. Child neurologists and neurophysiologists participating in the investigation will recruit participants and collect informed consent. Parents will be fully informed about the study during a counseling session, and an information sheet will be provided.

### 2.11. Statistical Methods

Data will be analyzed initially using descriptive statistics. Dichotomous data will be compared using the chi-square test and parametric or non-parametric inferential tests for continuous data will be used after evaluation on normal distribution/homogeneity of variance. The method proposed by Grizzle will be applied for testing treatment differences [20]. Considering that the study was designed as a 2 × 2 crossover, potential carry-over effects will be considered in the inferential model used for the analysis of the primary endpoint. A *p*-value ≤ 0.05 will be considered to be statistically significant. A 95% confidence interval for non-inferiority will be appropriately calculated. All analyses will be performed using SAS 9.4 software (SAS Institute Inc., Cary, NC, USA).

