## 2. Methods

### 2.1. Study Design

The proposed study is a monocentric randomized crossover non-inferiority trial. Patients will be randomly allocated in a 1:1 ratio to start the study with melatonin or sleep deprivation for hypno-induction to perform EEG recordings. Subjects who will be allocated to the first sequence (sequence 1, *n* = 15) will receive melatonin in period 1 and sleep deprivation in period 2, while subjects who will be allocated to the second sequence (sequence 2, *n* = 15) will receive the two interventions in the reverse order. A total of 60 EEGs will be obtained.

The Consolidated Standards of Reporting Trials (CONSORT) flow diagram is shown in Figure 1 [13].

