### 2.6. Secondary Outcome Measures

Secondary outcomes will be as follows:-Wake after sleep onset (time in minutes patients are awake after sleep onset, WASO).-Sleep duration (duration in minutes from the beginning of non-REM stage 2 sleeping to the time patients are roused at the end of the study or spontaneously wake).-Number of EEGs characterized by electroclinical seizures collected and classified according to the 2017 International League Against Epilepsy (ILAE) classification and terminology [15].-Interictal abnormalities defined as epileptiform spike density per hour.

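### The chi-square test named for dichotomous data does not fit the paired EEG-with-seizure outcome; a paired test should be named

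*Protocol article*

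**What the plan says.** Section 2.1 fixes the design: "The proposed study is a monocentric randomized crossover non-inferiority trial". The Abstract gives the number of patients: "30 patients will be randomized to receive 3–5 mg melatonin or sleep deprivation". Both sequences receive both interventions, so each patient has two recordings, and Section 2.1 gives the total: "A total of 60 EEGs will be obtained".

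Section 2.6 lists, among the secondary outcomes, "Number of EEGs characterized by electroclinical seizures collected and classified" by the ILAE scheme. The unit counted is the EEG, and each EEG either shows such a seizure or does not.

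Section 2.11 says "Dichotomous data will be compared using the chi-square test" and sets the threshold: a p-value "≤ 0.05 will be considered to be statistically significant". Two further sentences there bear on the point. One applies Grizzle's method to treatment differences without saying for which outcomes. The other brings carry-over into the model, but only for the primary endpoint, which Section 2.5 defines as a continuous latency. No paired test for a binary outcome is named anywhere.

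**The concern.** The ordinary chi-square test assumes that every observation in the table is independent. A table of intervention by seizure (yes or no) would hold 60 recordings from only 30 patients, with each patient in both rows. Section 2.3 requires stable seizure frequency and stable medication, so a patient with a seizure on one EEG is plausibly more likely than another patient to have one on the other EEG. That is positive within-patient correlation, and the unpaired test then uses too large a standard error.

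The Introduction makes interference of melatonin with seizure manifestations a stated aim, and the Discussion notes that sleep deprivation might raise the risk of eliciting seizures. A test that leans towards no difference could therefore let a real difference pass unnoticed. A test has been named and does not match the design, so this is not simply detail left to an analysis plan: a plan that followed Section 2.11 would carry the mismatch forward.

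**Working it through.** **Inputs from the protocol article.** 30 patients and two recordings each: 30 × 2 = 60 EEGs, as Section 2.1 states, so 30 per intervention. Threshold 0.05 (Section 2.11), taken as two-sided.

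**Inputs assumed.** The document gives no seizure rate and no within-patient correlation ρ. Everything below rests on assumed rates and on ρ of 0, 0.3 and 0.5.

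**Step 1: why the test is conservative.** With a common rate p and n pairs, the chi-square test uses the variance 2p(1−p)/n for the difference in proportions. The true variance is 2p(1−p)(1−ρ)/n. The real size of a nominal 5% test is therefore about 2 × [1 − Φ(1.96/√(1−ρ))]:

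- ρ = 0: 5.0%
- ρ = 0.3: 1.96/√0.7 = 2.343, giving 1.9%
- ρ = 0.5: 1.96/√0.5 = 2.772, giving 0.6%

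**Step 2: small-sample check with 30 pairs.** Let a = pairs with a seizure on both EEGs, b and c = pairs with a seizure on one EEG only, d = neither. For rates p1 and p2, P(both) = p1·p2 + ρ√[p1(1−p1)p2(1−p2)]; the other cells follow by subtraction. For example, at 20% versus 40% with ρ = 0.5, P(both) = 0.08 + 0.098 = 0.178, and the discordant cells are 0.022 and 0.222. The chance of p ≤ 0.05 is the sum of multinomial probabilities over all tables (a, b, c, d) that reject. Exact McNemar is the two-sided binomial test of b against c with probability 0.5. Mid-p subtracts the probability of the observed split from the exact p-value.

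| Assumed rates | ρ | Chi-square | McNemar, asymptotic | McNemar, exact | McNemar, mid-p |
|---|---|---|---|---|---|
| 20% vs 20% (size) | 0 | 4.9% | 4.3% | 2.2% | 4.1% |
| | 0.3 | 2.0% | 4.7% | 1.5% | 3.5% |
| | 0.5 | 0.7% | 4.8% | 0.8% | 2.35% |
| 20% vs 40% (power) | 0 | 39% | 37% | 28% | 37% |
| | 0.3 | 37% | 49% | 38% | 48% |
| | 0.5 | 34% | 67% | 49% | 62% |
| 5% vs 15% (power) | 0 | 26% | 23% | 10% | 18% |
| | 0.3 | 22% | 30% | 9% | 18% |
| | 0.5 | 18% | 34% | 8% | 18% |

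The chi-square sizes agree with Step 1.

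**Step 3: two invented tables, one in each direction.**

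- *Moderate counts, strong pairing.* Four patients have a seizure on both EEGs, six after deprivation only, none after melatonin only: 10/30 versus 4/30. The pooled rate is 14/60 = 0.233, so chi-square = 0.2² / (0.233 × 0.767 × 2/30) = 3.35, p = 0.067. Asymptotic McNemar: 6²/6 = 6.0, p = 0.014. Exact: 2 × 0.5⁶ = 0.031. Mid-p: 0.031 − 0.016 = 0.016.
- *Few events.* No patient has a seizure on both EEGs, four after deprivation only, none after melatonin only: 4/30 versus 0/30. The pooled rate is 4/60 = 0.067, so chi-square = 0.133² / (0.067 × 0.933 × 2/30) = 4.29, p = 0.038. Exact: 2 × 0.5⁴ = 0.125. Mid-p: 0.125 − 0.0625 = 0.0625.

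The choice of test can thus move the result across 0.05 either way.

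**Step 4: large-sample condition.** The expected number of seizure EEGs per intervention is half the total. With fewer than 10 seizure EEGs among the 60, it falls below 5 and the chi-square approximation is doubtful in any case.

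**The case against.** The strongest reply is that Section 2.11 never says the 60 recordings will be treated as independent. The chi-square clause directly follows the mention of descriptive statistics and shares its sentence with a generic rule for continuous data. The Grizzle sentence comes next and is not limited to one outcome. One could read the section as general or baseline tests first, then a crossover method for treatment comparisons, or take the chi-square to be McNemar's. This stands in part: independence is the ordinary reading of the test named, not the literal wording. But none of the alternatives is stated. Dichotomous data have already been given their own test, the Grizzle sentence mentions no binary outcome, and the carry-over sentence is confined to the continuous primary endpoint. If another reading is meant, a clarifying phrase is still needed.

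The second reply is that a paired test is not always the more powerful one. This stands. At 5% versus 15% the exact test has 8% to 10% power against 18% to 26% for chi-square, and at 20% versus 40% it is behind at ρ = 0, level at ρ = 0.3 and ahead only at ρ = 0.5. How often electroclinical seizures will occur in a one-hour nap recording is unknown from the document, so low counts are quite possible.

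The third reply is that the consequence is limited: this is one of four secondary outcomes, and the sample size in Section 2.8 was set for latency. This also stands.

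**Conclusion.** The point holds in a limited form. Section 2.11 names a test that, in its ordinary sense, ignores the pairing of the EEG-with-seizure outcome, and nothing else in the text supplies a paired analysis for it. With positive within-patient correlation the nominal 5% test works at about 2% (ρ = 0.3) or 0.7% (ρ = 0.5) for assumed rates of 20%. At an assumed 20% versus 40% with ρ = 0.5, it reaches about 34% power against 67% (asymptotic) or 49% (exact McNemar).

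A reader might infer three stronger things that the document does not support:

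- *That false claims of a difference become more likely.* Under positive correlation the error is conservative.
- *That the non-inferiority conclusion is compromised.* The primary endpoint is continuous and has its own crossover analysis.
- *That pairing would always rescue a significant result.* With few seizures or little correlation the paired p-value can be larger.

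The reason to change is a test whose error rate fits the design, not a promised gain in power. All sizes and powers depend on the assumed rates and correlations.

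**What to change.** In Section 2.11, limit the chi-square (or Fisher) test to comparisons between the two sequences. For dichotomous outcomes compared between interventions, name a paired test and a paired 95% confidence interval for the difference in proportions. McNemar with the mid-p value is a sensible choice, because the exact version is itself very conservative when events are few. If period is to be allowed for, use Mainland–Gart or Prescott, or a logistic model with a patient effect. State also whether the Grizzle sentence is meant to cover outcomes other than latency.

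The cost is a sentence or two. No new data, patients or design change are needed. The price to accept in advance is that, with few seizures or little correlation, the paired analysis may give a larger p-value than chi-square would, so the choice should be fixed before the data are seen.

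### Section 2.11 lets carry-over into the primary 2×2 crossover analysis; as a model term or a selecting pre-test, that does not match the full-crossover sizing in section 2.8

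*Protocol article*

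**What the plan says.** - Protocol article, 2.11 Statistical Methods: "The method proposed by Grizzle will be applied for testing treatment differences". For the primary endpoint, "potential carry-over effects will be considered in the inferential model used for the analysis of the primary endpoint". The section gives no form for the carry-over element, no pre-test level and no rule for what follows from it. Its general threshold is a p-"value ≤ 0.05 will be considered to be statistically significant", with no side stated, and it promises a 95% confidence interval for non-inferiority.
- Protocol article, 2.8 Sample Size Calculation: a non-inferiority crossover formula, 80% power, "a level of significance for a one-sided test of 0.025", and a limit for no relevant difference "between the study procedures is −3 min in the sleep latency onset". No SD, within-patient correlation or assumed true difference is given.
- Protocol article, Abstract and 2.1 Study Design: "30 patients will be randomized to receive 3–5 mg melatonin or sleep deprivation", 15 per sequence, 60 EEGs.
- Protocol article, 2.4 Interventions: one melatonin dose or one night of partial sleep deprivation, then "One–three months after the first EEG recording, the crossover will take place".

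**The concern.** A crossover is efficient because each patient serves as their own control, and section 2.8 relies on that efficiency. In a 2×2 design, carry-over cannot be separated from a difference between the sequence groups. A model that adjusts the treatment effect for carry-over therefore falls back on the between-patient comparison in period 1.

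Grizzle's method, as the name is commonly used, gets there in two stages: test carry-over on patient totals, then analyse period 1 alone if that test is significant. The totals and the period-1 values are correlated, so the fallback tends to be used when period 1 is unbalanced by chance.

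At stake is whether the only primary test has the power and the one-sided error rate for which the trial was sized.

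**Working it through.** **Inputs from the protocol article.** Margin 3 min, power 80% and one-sided 0.025 (2.8); 30 patients and 60 EEGs (Abstract); 15 patients per sequence (2.1). The figure of 30 per sequence in 2.8 fits if it counts EEGs (15 × 2).

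**Assumptions, because the documents give no figure.** True difference 0 for power; normal data; no true carry-over; within-patient correlation ρ shown as a range; pre-test level 5% or 10%. The margin is read as melatonin latency at most 3 min longer than after deprivation.

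**1. The planned figure.** Without an SD it cannot be reproduced, only solved backwards. With N = 2σw²(1.96 + 0.84)²/3² = 30, the within-patient SD is σw = 3√15/2.80 = 4.15 min (SD of paired differences 5.87 min). With a t-test on 28 df, 80% power needs σw = 4.00 min (SD of differences 5.66 min).

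**2. Which EEGs identify treatment.** Let τ be the treatment effect, π period and λ carry-over. The four cell means are:
- sequence 1: μ + τ, then μ + π + λ
- sequence 2: μ, then μ + π + τ

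Four parameters fit four means exactly, so τ is the first cell minus the third. The weights in the order sequence 1 (periods 1, 2), sequence 2 (periods 1, 2) are [1, 0, −1, 0]. Only 30 of the 60 EEGs count.

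Replace λ by a sequence effect on both cells of sequence 2, and the weights become [0.5, −0.5, −0.5, 0.5]. That is the full within-patient contrast.

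**3. Power with a carry-over term.** The planned variance is 2σw²/30. The period-1 variance is 2σw²/[15(1 − ρ)]. The ratio is 2/(1 − ρ), so power = Φ(2.80/√[2/(1 − ρ)] − 1.96). At ρ = 0.5 this is Φ(1.40 − 1.96) = 29%.

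| ρ | Variance ratio | Power |
|---|---|---|
| 0 | 2.0 | 51% |
| 0.2 | 2.5 | 43% |
| 0.3 | 2.9 | 38% |
| 0.5 | 4.0 | 29% |
| 0.7 | 6.7 | 19% |
| 0.9 | 20 | 9% |

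The t-based calculation at σw = 4.00 gives the same percentages. To keep 80% by this route would take about 62 patients at ρ = 0, 120 at 0.5 and 202 at 0.7.

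**4. Two-stage rule.** Simulation with t-tests on 28 df and σw = 4.00, 400,000 trials per setting. For the error rate the true difference is at the margin; for power it is 0.

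| ρ | Pre-test level | False non-inferiority | Same, within fallback trials | Power |
|---|---|---|---|---|
| 0 | 5% | 3.1% | 16% | 79% |
| 0 | 10% | 3.5% | 12% | 77% |
| 0.5 | 5% | 3.7% | 26% | 79% |
| 0.5 | 10% | 4.0% | 18% | 77% |
| 0.8 | 5% | 4.2% | 36% | 79% |
| 0.8 | 10% | 4.5% | 23% | 77% |

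The full crossover contrast in the same simulations gave 2.5% error and 80% power. The fallback column is already contained in the overall rate: at ρ = 0.5 with a 5% pre-test, 0.05 × 0.26 is about 1.3 of the 3.7 percentage points.

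**The case against.** The strongest reply is that 2.11 says only that carry-over will be considered. It states no pre-test, no fallback and no period-1 analysis, and a condensed article may leave the model terms to a fuller plan. A sequence term is an ordinary way to consider carry-over, and step 2 shows that it costs nothing. A descriptive carry-over check is equally harmless. The two-stage rule and its levels are not written in the article; they follow from the usual meaning of the method's name.

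Much of this stands. A reader might infer that the plan definitely builds in a carry-over adjustment, that every reading breaks the design, or that power is 29%. The documents support none of these: the wording is softer, two readings do no harm, and 29% needs a correlation of 0.5 that appears nowhere.

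The harms are also different in kind. With a carry-over term and no true carry-over, the estimate is unbiased and the error rate correct; only power is lost. With the two-stage rule, average power barely moves and the error rises by about 0.6 to 2.0 percentage points.

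What does not stand is treating this as mere missing detail. The article chooses a named method for the treatment test and places carry-over inside the primary model. Taken literally, that gives a worse analysis than the one used for sizing. It also leaves the choice between harmful and harmless forms unsettled for a confirmatory test.

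**Conclusion.** The concern holds in a limited form: section 2.11 does not match section 2.8 under either way in which carry-over could alter the primary result.

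- **Carry-over as a model term:** power is at most about 51% for any non-negative correlation, and lower as the correlation rises. That only period 1 is used is algebra; the percentages assume the SD that yields the planned 80%.
- **Carry-over as a selecting pre-test:** false non-inferiority is about 3.1–4.5% instead of 2.5%, with average power about 77–79% against 80%. This assumes a 5–10% pre-test, correlations from 0 to 0.8 and no true carry-over.
- **Carry-over only reported, or a sequence term only:** no harm.

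The design offers little to set against the cost of the first two. Each intervention is a single dose or a single night, and the periods are one to three months apart.

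**What to change.** Replace the two sentences in 2.11 on Grizzle's method and carry-over with a statement that:

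- the primary analysis is the within-patient melatonin minus sleep deprivation contrast in sleep onset latency, adjusted for period. It may be a two-sample comparison of period differences between sequences, or a mixed model with treatment, period and random patient, optionally with a sequence term;
- its two-sided 95% confidence interval is compared with the 3-minute margin, which matches the one-sided 0.025 in 2.8;
- there is no carry-over regressor, and no carry-over test selects the analysis;
- any sequence contrast is descriptive only.

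Give as the reason that the interventions are short and the interval is 1–3 months, so carry-over is implausible. Do not write that it is excluded: a treatment-by-period interaction has the same alias and the interval does not rule it out.

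The cost is two sentences and no new data. The one downside is that the primary estimate would not be adjusted if real carry-over or such an interaction existed.
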